### Data collection methods

#### Primary outcome

Patients will be followed-up by telephone regarding their survival status at each timepoint during the follow-up period, as shown in Fig. 2. After 3 years of follow-up of the last patient is complete, we will calculate the 3-year OS rate for both groups.

#### Secondary outcomes

For HRQoL, we will use the Constant–Murley scale to evaluate shoulder function at each follow-up timepoint. In order to improve the reliability of shoulder function evaluation, two clinicians will be systematically trained on use of the scale.

For PFS, observations will start at time of randomization and end when events (see below) occurred. In the period of time from randomization (Fig. 3) to any primary recurrence, local metastasis, distant metastasis, and other life-threatening events or death will be defined as PFS.

If a patient has not returned to the clinic for more than 2 months after the follow-up timepoint, a telephone inquiry will be conducted.

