#### Secondary outcomes

The secondary outcomes are HRQoL and progression-free survival (PFS). For HRQoL, we will use the Constant–Murley scale to evaluate patients’ shoulder function, with follow-up at 7 days, 21 days, 3 months, 6 months, 1 year, 2 years and 3 years after surgery.

There are many reasons for setting OS as the primary outcome. First, it is widely used as a reliable indicator for evaluating the prognosis of tumors. It is reported that the 3-year OS rate in an IIb dissection group is about 80% [1], which includes disease-free survival and living with disease. Metastasis in level IIb is extremely low, and even if it happens it is nonlethal and can be instantaneously controlled by surgery or radiotherapy. Theoretically, 3-year OS in the IIb retention group will resemble that in the dissection group. A summary of 38 RCTs [7, 23] reports no significant association between PFS duration and HRQoL. In addition, as PFS is not as reliable as OS and can also increase difficulties in follow-up, we did not use PFS as the primary outcome.

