### Sample size

In calculating the sample size, we assumed the 3-year OS rate in the IIb retention group will be about 78%, α = 0.05 (one-sided), power of 80% (β = 20), and that in the IIb dissection group will be 80% [1]. The noninferiority margin will be 12%, so the sample size as generated by PASS Sample Size Software 15.0 (NCSS LLC, Kaysville, Utah, USA) will be 261 for IIb retention and 260 for IIb dissection. To obtain a reasonable sample size and make sure the trial is instructive for clinical work, we combined the common opinions of oral and maxillofacial experts, and the statistician defined the noninferiority margin as 12% [24]. Although the value seems to be large, its role is to control the large sample size that would otherwise be unapproachable.

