#### Progression-free survival

We will use a two-sided log-rank test to check the difference in PFS between the two groups.

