### Adverse events

Patients will be informed of all the surgical risks and adverse effects of intervention before surgery, which will be performed only if informed consent is signed. The Ethics Committee of Shanghai Ninth People’s Hospital will be notified of any adverse events (such as hemorrhagic shock, myocardial infarction, or death) that occur during surgery.

Primary recurrence or neck/distant metastasis (bone or lung) may occur in both groups. We will expand tumor resection if a primary recurrence occurs and perform radiotherapy or neck dissection depending on the tumor size. If IIb metastasis is detected during follow-up in the retention group, we will dissect level IIb and perform radiotherapy if necessary. If level IV or V is affected, we will perform additional ipsilateral or bilateral neck dissection, plus radiotherapy or chemotherapy later if needed.

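### PFS counts undefined life-threatening events as well as death, so a survived operative or medical event would, as worded, count as progression

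*Protocol article*

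**What the plan says.** Under Data collection methods, Secondary outcomes, the article says of PFS that "observations will start at time of randomization and end when events (see below) occurred". It then lists the events: the period from randomization "to any primary recurrence, local metastasis, distant metastasis, and other life-threatening events or death will be defined as PFS".

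The life-threatening category is not defined there or elsewhere in the article, and it stands beside death as a separate item.

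Participant timeline puts randomization before the operation. The Adverse events section requires the ethics committee to be told of "any adverse events (such as hemorrhagic shock, myocardial infarction, or death) that occur during surgery".

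PFS is a secondary outcome. Its analysis, under Statistical methods, Progression-free survival, is one sentence: "We will use a two-sided log-rank test to check the difference in PFS between the two groups". The article states no margin, event rate or power for PFS.

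**The concern.** PFS is meant to show whether the cancer is controlled. Of the outcomes the article names, it is the one that registers a recurrence in a retained level IIb directly. The Outcomes section itself argues that such a recurrence is rarely fatal, so overall survival may not show it.

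Death from any cause is a normal PFS component and is not at issue. The objection is to the non-fatal events added beside it. A patient who survives an operative cardiac event and stays free of tumour would be counted as having progressed on the day of surgery. A neck recurrence in that patient two years later would no longer enter the endpoint.

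Two things are at stake. First, the PFS hazard ratio no longer estimates the effect on tumour control, and the distortion depends on event rates that nobody has stated. Second, no criterion says what counts as life-threatening, while surgeons and patients know the allocation.

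**Working it through.** **The wording**

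1. The clock starts at randomization and surgery follows, so operative events fall inside the PFS period.
2. The event list has death and, separately, other life-threatening events. The second item can only add events that the patient survives.
3. The Adverse events section names two such events that are not tumour events: hemorrhagic shock and myocardial infarction.
4. Observation ends at the first listed event, so a later recurrence in the same patient is not counted.

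**Size**

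The article has no PFS figure to reproduce, so this is an illustration.

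*From the article:* level IIb metastasis of no more than 6% (Background); 261 and 260 patients (Sample size); a two-sided log-rank test.

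*Assumed:* 30% three-year tumour events or deaths with dissection; a true hazard ratio (retention against dissection) of 1.25; unrelated non-fatal events with three-year probability x; constant, independent hazards; three years of follow-up for each patient; a two-sided 5% level for PFS.

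*Why 1.25:* 1 − 0.70^1.25 = 0.360, an excess of 6.0 points over 30%. That is about what would follow if every level IIb metastasis at the stated upper limit became an additional event.

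*Cumulative hazards over three years:* H0 = −ln 0.70 = 0.3567; H1 = 1.25 × 0.3567 = 0.4458; Hx = −ln(1 − x).

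*Observed hazard ratio:* (H1 + Hx) / (H0 + Hx).

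*Events:* E = 261 × [1 − exp(−(H1 + Hx))] + 260 × [1 − exp(−(H0 + Hx))].

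*Power:* Φ(√(E × 261 × 260 / 521²) × ln HR − 1.96).

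| x in each arm | Hx | Hazard ratio | Events | Power |
|---|---|---|---|---|
| 0 | 0 | 1.25 | 172 | 31% |
| 2% | 0.0202 | 0.4660 / 0.3769 = 1.24 | 179 | 29% |
| 5% | 0.0513 | 0.4971 / 0.4080 = 1.22 | 189 | 27% |
| 8% | 0.0834 | 0.5292 / 0.4401 = 1.20 | 200 | 26% |

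With a base of 20% instead of 30%, the same x values give 1.23, 1.20 and 1.18.

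**Unequal rates** (30% base)

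- 2% with retention and 5% with dissection: (0.4458 + 0.0202) / (0.3567 + 0.0513) = 1.14.
- 5% with retention and 2% with dissection: (0.4458 + 0.0513) / (0.3567 + 0.0202) = 1.32.

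A difference between arms moves the estimate more than equal rates do, and it can move it either way.

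**The case against.** **Other may mean other tumour events.** The item follows recurrence and metastasis, so it could be read that way. The text does not say so, and two readers could code the same patient differently. The intended reading needs to be written down.

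**The article is condensed.** Detailed definitions and adjudication may sit in a full protocol or analysis plan that is not shown. That would answer a complaint about missing detail. Here the event list is stated, and a later document would either inherit it or contradict it.

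**Operative events may never reach PFS.** The article handles them as adverse events and does not link them to PFS. Participant timeline, Intervention, also subtracts patients removed during surgery before follow-up begins. So some of these patients may leave the trial instead of being counted. This does not narrow the definition for those who stay, or for medical events after surgery.

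**A blinded evaluator is planned.** The Blinding section says the statisticians and the evaluator will not know the groups. This weakens any claim of biased classification, although the events are first recorded by staff who know the allocation and no written criterion exists.

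**Losing later events is normal.** Any time-to-first-event endpoint does this. True, but the event that ends observation should then belong to the endpoint.

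**PFS has little power anyway.** In the illustration power is 31% without the extra events and 26% to 29% with them. Removing them hardly changes what the test can detect. This stands, and it limits the severity.

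A reader might infer that the wording must hide harm from leaving level IIb in place. The documents do not support that. They give no event rates by arm, and more events with retention would exaggerate harm. A larger illustration, such as a true hazard ratio of 1.50, also fits poorly: 1 − 0.70^1.5 = 0.414, an excess of 11.4 points against a stated level IIb rate of no more than 6%.

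**Conclusion.** The point holds, at minor to moderate severity. As written, PFS counts survived life-threatening events whether or not they concern the tumour, and the operative events named in the article meet that wording.

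With equal rates of 2% to 8% in both arms, an assumed hazard ratio of 1.25 becomes 1.24 to 1.20. With rates of 2% and 5% in opposite arms it becomes 1.14 or 1.32, depending on which arm has more. All of this rests on assumed rates and constant hazards. If such events are rare, the effect is negligible.

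A reader might also infer that the non-inferiority conclusion is at risk. It is not: the margin and sample size concern overall survival, which this definition does not touch. What is affected is the interpretation of PFS as a measure of tumour control.

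**What to change.** Define PFS as the time from randomization to the first of local recurrence, regional (neck, including level IIb) recurrence, distant metastasis, or death from any cause. Delete the life-threatening-events item, and report non-fatal life-threatening events by arm as safety outcomes.

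The cost is one sentence and slightly fewer PFS events: in the illustration 172 instead of 179 to 200, so 7 to 28 fewer, none of them tumour events or deaths. Under Trial status, the article says that enrolment had not begun at this version, so the change could be made before any patient was randomized.

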### Data management

All paper versions of the original materials will be photographed and saved in an encrypted database. All electronic data will be stored in the electronic medical records of the Shanghai Ninth People’s Hospital. All procedures for evaluating shoulder function will be filmed and saved.

### Statistical methods

#### Overall survival

This trial will be terminated when the last patient has been followed-up for 3 years. After the trial ends, the primary endpoints will be tested by means of two-sided log-rank tests.

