**Methods:**

We designed a parallel-group, randomized, non-inferiority trial that is supported by Shanghai Ninth People’s Hospital, Shanghai Jiao Tong University, School of Medicine, Shanghai, China. We will enroll 522 patients with early oral carcinoma who match the inclusion criteria, and compare differences in 3-year overall survival, progression–free survival (PFS) and HRQoL under different interventions (retention or dissection of level IIb). The primary endpoints will be tested by means of two-sided log-rank tests. Analysis of overall and progression-free survival will be performed in subgroups that were defined according to stratification factors with the use of univariate Cox analysis. In addition, we will use post-hoc subgroup analyses on the basis of histological factors that were known to have effects on survival, such as death of invasion of the primary tumor. To evaluate HRQoL, we will choose the Constant–Murley scale to measure shoulder function.

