## Methods

### Study aims and design

Before designing this protocol, we searched the PubMed database for randomized controlled trials (RCTs) of IIb neck dissection in early-stage oral cancer on 30 May 2018, but we found no results. We repeated the search on 26 November 2018 using the keywords “IIb” and “neck” and searching only in English. We found only one RCT with a small sample size from 2018, and six prospective analyses of IIb after neck dissection from 2004 to 2018. In addition, we found two retrospective systematic reviews and meta-analyses. All of the above indicated that the rate of IIb metastasis in early-stage oral cancer is extremely low at no more than 6%. However, there is still no strong evidence to prove the necessity of IIb dissection in T1–T2N0M0 OSCC.

We are conducting a parallel-group, noninferiority randomized trial to assess whether IIb neck dissection should be performed in T1–T2 N0 OSCC and its impacts on OS and HRQoL. Our study plan is summarized in Fig. 1.

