### Outcomes

#### Primary outcome: overall survival (OS)

We will use the 3-year OS after surgery as the primary outcome, and follow-up at 3 months, 6 months, 1 year, 1.5 years, 2 years, 2.5 years and 3 years after surgery (Fig. 2).

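### The stated primary test, a two-sided log-rank test for a difference, never uses the 12-point margin, so the analysis as written cannot establish non-inferiority

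*Protocol article*

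**What the plan says.** Study aims and design declares the objective: "We are conducting a parallel-group, noninferiority randomized trial to assess whether IIb neck dissection should be performed". Outcomes sets the endpoint: "We will use the 3-year OS after surgery as the primary outcome". Sample size assumes 3-year OS of 78% with IIb retention and 80% with dissection, a one-sided alpha of 0.05 and 80% power, and continues: "The noninferiority margin will be 12%, so the sample size as generated by PASS Sample Size Software 15.0" gives 261 and 260 patients.

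Statistical methods, Overall survival, then states the analysis: "the primary endpoints will be tested by means of two-sided log-rank tests". The Methods part of the Abstract repeats it. The only other statement on how OS is handled is in Data collection methods, Primary outcome: "we will calculate the 3-year OS rate for both groups". The margin appears nowhere outside Sample size. For progression-free survival (PFS) the plan is: "We will use a two-sided log-rank test to check the difference in PFS between the two groups".

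**The concern.** The design and the stated test differ in three respects.

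- **Hypothesis.** The design's null is that retention is worse by 12 points or more. The log-rank null is a hazard ratio of 1.
- **Sidedness.** Sample size is one-sided; the test is two-sided.
- **Scale.** Endpoint and margin are on the 3-year rate; the log-rank test compares whole survival curves.

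A non-significant log-rank p-value is not evidence of non-inferiority, and a significant one answers a different question. The trial would end without a test of its own objective. The tempting substitute, taking p > 0.05 to mean not inferior, has an error rate that nothing in the plan controls and that rises as information is lost. The temptation is real: Secondary outcomes says that survival in the retention group should in theory be close to that in the dissection group, so a non-significant result is what the authors expect.

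**Working it through.** **Inputs.** From Sample size: OS 80% (dissection) and 78% (retention), margin 12 points, power 80%, 261 and 260 patients. Assumptions: the margin is absolute, so retention at the margin is 80% − 12% = 68%; survival is exponential; follow-up is 3 years with no loss.

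**Step 1: reproduce the sample size.** For non-inferiority of two proportions with unpooled variance,

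n per arm = (z_α + z_β)² × [p₁(1−p₁) + p₂(1−p₂)] / (margin − expected deficit)²

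- Variance sum: 0.78×0.22 + 0.80×0.20 = 0.3316. Denominator: (0.12 − 0.02)² = 0.01.
- One-sided 0.025: (1.960 + 0.842)² × 0.3316 / 0.01 = 260.3, so 261. This matches.
- One-sided 0.05, as stated: (1.645 + 0.842)² × 0.3316 / 0.01 = 205.01, so 206. This does not match.

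The trial was therefore sized for a margin test on the difference in 3-year rates, and the stated number corresponds to one-sided 0.025.

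**Step 2: behaviour of the stated test.** With HR = ln(S_ret)/ln(S_dis) and D = 261(1−S_ret) + 260×0.20 deaths, the log-rank statistic has mean about θ = ln(HR)×√(D/4), and the test rejects with probability Φ(θ − 1.96) + Φ(−θ − 1.96). At the margin: HR = ln 0.68/ln 0.80 = 1.728, D = 83.5 + 52 = 135.5, θ = 0.547 × 5.82 = 3.18, rejection 89.0%, non-significance 11.0%.

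The margin test succeeds with probability Φ((0.12 − deficit)/SE − z).

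| True OS, retention vs dissection | HR | Deaths | Log-rank non-significant | Margin test succeeds, one-sided 0.025 | Margin test succeeds, one-sided 0.05 |
|---|---|---|---|---|---|
| 78% vs 80% | 1.113 | 109.4 | 91.3% | 80.0% | 87.7% |
| 74% vs 80% | 1.349 | 119.9 | 62.5% | 37.1% | 49.5% |
| 72% vs 80% | 1.472 | 125.1 | 42.0% | 18.8% | 28.4% |
| 68% vs 80% | 1.728 | 135.5 | 11.0% | 2.5% | 5.0% |

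Simulation (4,000 trials per scenario, log-rank test and 95% interval on the same data) agrees: non-significance of 92.0%, 43.1% and 11.8% at true retention OS of 78%, 72% and 68%, with margin-test success of 79.7%, 19.2% and 2.8%.

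Only the 68% row measures a false claim of non-inferiority. In the 72% and 74% rows the deficit lies inside the margin; they show how far the two tests disagree.

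**Step 3: effect of losing information.** Log-rank non-significance at a true 68% vs 80% is 11.0% with 261 per arm, 19.2% with 206 and 49.5% with 100. A valid margin test would hold its error at the nominal level throughout.

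**Step 4: where the two rules part.** At the design assumption SE = √(0.78×0.22/261 + 0.80×0.20/260) = 3.57 points. A difference is significant, approximately, when the observed deficit exceeds 1.96 × 3.57 = 7.0 points. Non-inferiority at one-sided 0.025 needs a deficit below 12 − 7.0 = 5.0 points. Observed deficits between about 5 and 7 points are thus non-significant yet fail the margin. At 78% vs 80%, 12.9% of simulated trials were non-significant without showing non-inferiority.

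**Step 5: would a hazard-ratio margin do?** Keeping the log-rank framework but shifting the null to HR 1.728 gives power Φ(ln(1.728/1.113) × √(109.4/4) − z) = Φ(2.30 − z): 63% at one-sided 0.025 and 74% at one-sided 0.05. Both fall short of 80%.

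**The case against.** The strongest reply is that this is a condensed article. It fixes the margin and promises the 3-year OS rate in each group, which are the ingredients of a margin comparison; the interval method and decision rule may sit in an analysis plan that is not shown. That would answer a complaint about omission. But the article is not silent: it names the primary test twice, and that test contradicts the design. An analysis plan with a margin test would conflict with the article, which would still need correcting. A margin-shifted log-rank test exists, but a two-sided test with no margin hazard ratio cannot be read as one.

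Some narrower points stand:

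- The article nowhere says that p > 0.05 will be taken as non-inferiority. The 11% is conditional on that reading.
- PFS is secondary and has no stated margin, so a test of difference is coherent there. The PFS point is subsidiary: a non-significant result must not be presented as evidence of equivalence.
- A hazard-ratio margin is a legitimate method. The case for the difference scale is that the trial was sized on it and a hazard-ratio margin would be underpowered.
- A 95% interval implies one-sided 0.025, whereas Sample size states one-sided 0.05. The interval cannot be fixed without settling this.

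**Conclusion.** The concern holds: the primary analysis is wrong as written. The stated test does not use the margin and cannot establish non-inferiority. At the design assumption it rejects in 8.7% of trials (8.0% simulated), so it does not carry the planned 80% power for the trial's aim. If non-significance were taken as non-inferiority, the false-claim rate at the margin would be about 11% to 12%, more than twice 5% and over four times 2.5%. These sizes rest on an absolute margin, exponential survival and complete 3-year follow-up; the mismatch between test and objective depends on none of them. Because it concerns the trial's main conclusion, it must be corrected before analysis.

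**What to change.** In Statistical methods, Overall survival, and in the Abstract:

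1. Define the primary analysis as the difference in Kaplan-Meier 3-year OS, retention minus dissection, with Greenwood variance and a two-sided 95% confidence interval. Claim non-inferiority only if the lower limit lies above −12 percentage points.
2. Reconcile alpha in Sample size. The 261 and 260 patients match one-sided 0.025 and hence the 95% interval, with 80.0% power and 2.5% error at the margin. If one-sided 0.05 is really intended, the interval is 90%, with 87.7% power and 5.0% error at the same numbers.
3. Keep the log-rank test as a supporting test of superiority, and state that a non-significant p-value is not evidence of non-inferiority.
4. Report PFS as a difference or hazard ratio with a confidence interval, under the same caution.

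The cost is wording in the protocol and analysis plan. No extra patients or data are needed.

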#### HRQoL

We will use a repeated analysis of variance (ANOVA) measure to analyze changes in Constant–Murley score between the two groups. It is reported that about 67% of patients have shoulder syndrome after neck dissection even if the accessory nerve is spared [26]. Currently, two methods might work to deal with the problem of shoulder dysfunction. The first is to restore the damaged nerve with such methods as intraoperative brief electrical stimulation of the spinal accessory nerve (BEST SPIN). However, this technique has little effect [27], and literature on the treatment of damaged accessory nerves is rare. The second is retention of level IIb during surgery to preserve the integrity of accessory nerve function and structure. By measuring changes in the action potential of the accessory nerve during surgery it was found that level IIb dissection can greatly damage the accessory nerve [6]. We will use the Constant–Murley scale [28] to assess shoulder function. Although the scale’s reliability in evaluating shoulder function has been questioned [29], it has been clinically applied for more than 30 years, and it can reflect both subjective indicators (such as pain or daily activity) and objective standards (such as the muscle mobility and power). Because of the tissue defect caused by primary resection, distant free or adjacent flaps are used to restore it. In order to ensure the flaps are alive, movement control after surgery is crucial. Patients with free flaps are clinically permitted to lift the upper body on the fifth day after surgery and can also sit up in bed. On the sixth day after surgery, mild activities such as walking are permitted. Therefore, the first timepoint for evaluating shoulder function will be the seventh day after surgery, and then there will be follow-up at 1 month, 6 months, 1 year, 2 years and 3 years.

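### Repeated-measures ANOVA of shoulder scores to 3 years, in its classical form, can use at most about 412 of 521 patients on the trial's own survival assumptions

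*Protocol article*

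**What the plan says.** The HRQoL part of the Statistical methods section gives the analysis of shoulder function in one sentence: "We will use a repeated analysis of variance (ANOVA) measure to analyze changes in" the Constant–Murley score between the groups. The same section starts assessment on day 7 and continues with "follow-up at 1 month, 6 months, 1 year, 2 years and 3 years", which makes six visits. The Secondary outcomes section under Outcomes lists seven, "with follow-up at 7 days, 21 days, 3 months, 6 months, 1 year, 2 years and 3 years after surgery". Both lists end at 3 years.

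The Sample size section supplies the survival assumptions: "we assumed the 3-year OS rate in the IIb retention group will be about 78"% and "that in the IIb dissection group will be 80"%, with 261 and 260 patients.

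The article does not say how a death or a missed visit enters the shoulder analysis. The Follow-up section counts patients who leave during follow-up separately from the number analysed. The Data collection section provides a telephone inquiry when a patient is more than 2 months late for a visit.

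**The concern.** Classical repeated-measures ANOVA needs a complete row of scores for each patient. A patient who dies in year 3 has no 3-year score, so that patient's scores from day 7 to year 2 leave the analysis as well. Who stays in is then decided after randomization, partly by the trial's own primary outcome.

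This matters because better shoulder function is the reason the article gives for retaining level IIb, and a 12-point survival margin is accepted alongside it. A benefit estimated only in fully attending 3-year survivors does not describe the groups that were randomized, and it wastes usable data.

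A smaller issue is sphericity. The gaps between visits run from two or three weeks to a year, so equal variances of all between-visit differences are doubtful. That assumption bears on the group-by-visit test, which is the test of whether change differs between arms.

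**Working it through.** **The plan's own figure.** The article states no sample size or attrition figure for the shoulder analysis. The only figure to reproduce is the one for overall survival. Its inputs are "α = 0.05 (one-sided"), "power of 80% (β = 20"), "The noninferiority margin will be 12"%, and survival of 78% and 80%. With

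n per arm = (z₁₋α + z₀.₈)² × (0.78×0.22 + 0.80×0.20) / (0.12 − 0.02)²

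- one-sided α = 0.05: (1.645 + 0.842)² × 0.3316 / 0.01 gives 206 per arm;
- one-sided α = 0.025: (1.960 + 0.842)² × 0.3316 / 0.01 gives 261 per arm.

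So 261/260 matches one-sided 0.025 and not the stated 0.05. That is a separate matter. The 21% below comes from the survival rates and does not depend on it.

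**Ceiling on complete series.** Inputs are the arm sizes and survival rates from the Sample size section.

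- Deaths by 3 years, retention: 261 × 0.22 = 57.4
- Deaths by 3 years, dissection: 260 × 0.20 = 52.0
- Total: 109.4 of 521 = 21.0%
- Alive at 3 years: 521 − 109.4 = 411.6, about 412

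With the 522 patients of the Abstract (261 per arm) the result is 109.6 deaths, again 21.0%.

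**Scores discarded.** The article does not give the timing of deaths. Assuming a constant hazard, the proportion dead by year t is 1 − 0.78^(t/3) or 1 − 0.80^(t/3).

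| Visit | Dead, retention | Dead, dissection | Expected dead | Of the 109 deaths, still alive at this visit |
|---|---|---|---|---|
| 6 months | 4.1% | 3.7% | 10.6 + 9.5 = 20.1 | about 89 |
| 1 year | 7.9% | 7.2% | 20.7 + 18.6 = 39.4 | about 70 |
| 2 years | 15.3% | 13.8% | 39.8 + 35.9 = 75.8 | about 34 |

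On that assumption about 89 patients could have scores through 6 months that a complete-row analysis would not use.

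**Missed visits.** No rate is given, so these are illustrations only. If 5%, 10% or 20% of survivors miss at least one visit, the total loss is 1 − 411.6 × (0.95, 0.90, 0.80)/521 = 25.0%, 28.9% or 36.8%. If each visit is missed independently with probability 1%, 2% or 5%, the loss is 25.6%, 30.0% or 41.9% with six visits and 26.4%, 31.4% or 44.8% with seven. Misses that cluster in the same patients would lower these figures.

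**The case against.** The strongest reply is that exclusion is inferred. A reader might take the article to say that patients who die or miss a visit are dropped. It does not say so. One condensed sentence names a method, and a fuller analysis plan could specify a likelihood-based model. The separate count of patients who leave hints at analysing completers but does not settle it. This stands, so the point is conditional on the classical form of the method. It does not remove the point, because the method is named and nothing shown offsets its usual consequence.

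Other stronger readings also fail:

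- **A fixed loss well beyond 21%.** Any such number needs a missed-visit rate that the article does not give, and it also depends on which of two conflicting schedules applies.
- **Loss of the scores that matter most because nerve injury is greatest early.** The article does not say this. It explains day 7 by when patients may move after flap surgery.
- **Unreliable p-values throughout.** Sphericity concerns the within-patient tests only; the between-group main effect does not need it. A Greenhouse–Geisser correction or the multivariate form deals with it, though neither restores excluded patients.
- **A strong bias between arms.** Assumed deaths are 22% and 20%, so these figures alone suggest little differential selection by death.

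The loss of precision is also modest. At 80% power and two-sided 0.05 for a single comparison, the detectable standardized difference is 2.80 × √(2/261) = 0.25 with full arms and 2.80 × √(2/206) = 0.28 with about 206 per arm. Shoulder function is a secondary outcome with no sample size of its own.

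Finally, a mixed model does not solve the problem of death by itself. Under missing-at-random it implicitly extrapolates scores beyond death, and any late contrast among patients alive is again among survivors. The fix has to deal with this.

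**Conclusion.** The concern holds in conditional form. If the repeated-measures ANOVA is run classically to 3 years, deaths alone cap the analysis at about 412 of 521 patients, a loss of 21% on the trial's own assumptions, and any missed visit adds to it. The main damage is to what is being compared (3-year survivors with full attendance in place of the randomized groups) and to the earlier scores thrown away; the loss of power is smaller. Doubtful sphericity is secondary and correctable.

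The 21% rests only on the stated survival rates and arm sizes. The split by visit rests on an assumed constant hazard. This should be changed, but it concerns a secondary outcome and does not affect the primary survival analysis.

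**What to change.** Replace the ANOVA with a mixed model for repeated measures that uses every observed Constant–Murley score:

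- visit as a category, group-by-visit interaction and unstructured covariance, which also removes the sphericity assumption;
- T stage and primary subsite as covariates, since they are the stratification factors;
- one early visit, named in advance, as the main contrast, when few patients have died. The 6-month and 1-year visits are on both shoulder schedules, with about 4% and 7–8% expected dead under a constant hazard; the choice is for the trial team.

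State that scores after death are not a target of estimation. Treat late-visit contrasts as descriptive among patients alive, for example with a check restricted to those alive at that visit.

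Reconcile the two shoulder-visit schedules: Secondary outcomes has 21 days and 3 months where the HRQoL section has 1 month. The model needs one fixed set of visits.

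The cost is a change of wording, slightly more analysis work and a missing-at-random assumption for missed visits. No extra patients or measurements are needed for the model itself. The Trial status section says that enrollment had not started, so the change could be made before any data existed.
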